#### 2.4.2. Feasibility Analysis of the Intervention

The qualitative data will provide a more detailed insight into the perspective of relatives of patients with Parkinsonism as potential future primary caregivers. Qualitative, semi-structured interviews will be conducted at two time points via an online consultation with relatives immediately after the intervention (t1) and 6 weeks post-intervention (t2). This part of the feasibility analysis is structured by the three outcome aspects of acceptance, fit, and subjective benefit with corresponding operationalizations and queried in the interviews. The interview guide contains questions on acceptance, fit, and personal benefit of the intervention.

All interviews at t1 and t2 will be recorded and transcribed following data collection and stored for 10 years. During transcription, the ruleset suggested by Dresing and Pehl [59] will be followed. The spoken content is prioritized accordingly, while information on para- and non-verbal events are omitted. The MAXQDA 2020.4 software will be used for qualitative content analysis according to Kuckartz [60] using a combined model of deductive (a priori) and inductive coding (on the text material).

#### 2.4.3. Feasibility of the Intervention Manual

Not only the feasibility and impact of the intervention but also the manual adherence will be assessed quantitatively using an evaluation scheme developed for this purpose. Each section will be listed to independently rate whether the respective topic was addressed, as well as whether the worksheets provided were discussed. The scale consists of 14 items (10 topics, 4 worksheets) that are answered on a 4-point Likert scale ranging from 0 (not addressed) to 3 (fully addressed). A sum score will be obtained at the end to quantify adherence. Further topics addressed outside the manual will be noted. The manual adherence ratings will be completed by an independent rater using tape recordings of the sessions. This also allows noting deviations from the intervention time (50 min per session). The participant’s audio track will not be recorded and evaluated; only the advisor’s track will be recorded via the microphone output. However, all participants give their prior consent to these recordings.

With the help of feedback from the relatives, the feasibility of the intervention is evaluated. Therefore, the workbook also functions as an intervention diary. Before each session, the mood and motivation of the relatives are recorded. Except for the first session, they are asked what they remember of the previous session and if it was of any use to them. After each session, the relatives’ mood and satisfaction with the session are assessed by asking them how helpful they found the content and delivery of the intervention. The data are collected using a six-point Likert scale ranging from 0 (not at all) to 5 (very much).

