The intervention itself is solely aimed at the non-caregiving relatives and intends to strengthen resources, thereby fostering empowerment in the course of a progressive disease. Topics of the intervention, which follows a cognitive–behavioral therapy approach, are, on the one hand, the visualization and activation of relatives’ social network of relationships, and, on the other hand, specific exercises with relatives of people with Parkinsonism to empower dealing with stressful situations possibly arising in the future. The intervention is offered online and allows participation from home to facilitate implementation into relatives’ everyday life. The key question is, therefore, a threefold feasibility analysis:Feasibility of the intervention: the feasibility will be assessed via acceptability, fit and subjective benefit.Feasibility of the manual (adherence): it is to be assessed whether all planned aspects of the intervention have been discussed or if there are other topics that will be brought up by the relatives.Feasibility of the study design: investigating the feasibility of the study design means critically reflecting on the mixed-methods approach, the process of a baseline measurement with post and follow-up assessments, as well as the validity of the questionnaire selection and the structure of the interview guide. The data from questionnaires will be used for exploratory analyses.

Against this background, the primary aim of this multicenter pilot trial following a mixed-methods approach is to develop and assess the feasibility of a preventive psychological short intervention to relatives of patients with Parkinsonism at early stages. In addition, the secondary aims are to investigate the effects and manual adherence of the intervention.

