## 3. Discussion

Currently, there is limited evidence on the feasibility and effects of interventions for family members of people with Parkinsonism. The existing offers for relatives mostly have a psychoeducational orientation and refer to relatives of patients in a more advanced phase [18,26,27]. There are also approaches offering CBT treatments [28], but these can be quite time-consuming and do not have a preventive focus. Digital support programs based on telemedicine are currently still very rare, but they exist, for example, as a model of a telephone self-help group [30]. However, there are no outreach or preventive programs that specifically address relatives of patients in the early phase of the disease. The aim of the present study is, therefore, to develop a PPSI for relatives of people with Parkinsonism and to determine whether the target group accepts it, and the feasibility regarding its preventive approach and digital implementation is of particular interest. Furthermore, the fit of PPSI and the relatives’ needs, as well as their subjective benefit from the intervention in the current state, should give valuable feedback on which topics to add or remove in a future modified version of the preventive support offer.

Due to the multidimensional character of the burden that relatives of people with Parkinsonism are confronted with, and the rather high sense of stress at the time of diagnosis, implementing a PPSI with similar objectives appears to be an important approach.

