**Relatives**				
Sociodemografic data	Personal data	x		
Montreal Assessment (Moca) Blind 8.1	Cognition	x		
Parkinson’s disease caregiver burden questionnaire (PDCB)	Burden on family carergiver	x	x	x
Zarit Burden Interview (ZBI)	Burden on family carergiver	x		
Beck Depression inventory (BDI-II)	Depression	x	x	x
Health-related quality of life (EQ-5D)	Health-related quality of life	x	x	x
Coping Inventory for Dealing with Stressful Situations (CISS)	Coping strategies for stressful situations	x	x	x
Questionnaire on Health-Related Resources and Self-Management Skills (FERUS)	Health-related self-management strategies	x	x	x
Therapy Expectancy and Evaluation Questionnaire (PATHEV)	Therapy Expectancy	x	x	
Big-Five-Inventory 10 (BFI)	Personality	x		
Subjective Benefit (Credibility/Expectancy Questionnaire (CEQ))	Subjective Benefit		x	
Semi-structured Interview	Feasibility of the intervention		x	x

**Table 2 brainsci-12-00442-t002:** Feasibility analysis.

Outcome	Measurement Instruments	Operationalisation
Feasibility of the Intervention		
Acceptance	Interview	Willingness of the target group to participate
		Reasons for participation
		Evaluation of the digital intervention
Fit	Interview	Scope of the intervention
		Effort for the relatives
		Choice of timing
		Suggestions for optimization
		Overall assessment
Subjective Benefit	Interview	Particularly helpful aspects
		Psychosocial changes that the relatives notice about themselves
Evaluation of the intervention	Questionnaire (Filled in by the relative)	Questionnaires for the evaluation of each session
Feasibility of the intervention manual		
Adherence	Questionnaire (Filled in by Advisor)	Assess whether all intended aspects of the intervention have been discussed. A maximum of 14 points can be achieved
Feasibility of the study design		
Quality criteria	Expert panel	Quantiative: Validity, reliability, objectivity Qualitative: Transparency, intersubjectivity, range Drop-Out-Analysis

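### Manual feasibility asks whether every planned aspect was discussed, but the only derived value is a sum of 14 ratings from 0 to 3, which cannot show this over most of its range

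*Protocol article*

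**What the plan says.** The Introduction of the protocol article splits the key question into three feasibility parts. For the manual, "it is to be assessed whether all planned aspects of the intervention have been discussed", along with any other topics that relatives raise. The Adherence row of Table 2 repeats the question and adds a maximum: "Assess whether all intended aspects of the intervention have been discussed. A maximum of 14 points can be achieved".

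Section 2.4.3 describes the form. The ratings are made section by section: "Each section will be listed to independently rate whether the respective topic was addressed", and the worksheets are rated likewise. On length, "The scale consists of 14 items (10 topics, 4 worksheets"). The response format is a "4-point Likert scale ranging from 0 (not addressed) to 3 (fully addressed"). The one value derived from these ratings is the total: "A sum score will be obtained at the end to quantify adherence". The section also has off-manual topics and departures from the planned session time noted. It states no count of omitted items, no minimum per item and no cut-off.

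**The concern.** The question concerns every item: one planned aspect left out is enough to make the answer no. An unweighted sum is compensatory, so thorough treatment of some topics makes up for topics never reached. The value that the plan derives is therefore not the quantity that it defines.

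Feasibility of the manual is one of the three named parts of the key question, and the Conclusions plan to modify the intervention before a randomized trial. A topic or worksheet that advisors repeatedly fail to fit in is exactly what a manual check should reveal. In the total, such an element costs at most three points per relative, and the total does not say which element it was.

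**Working it through.** **Inputs.** From section 2.4.3: 14 items (10 topics + 4 worksheets), each rated 0 to 3, with 0 meaning not addressed and 3 meaning fully addressed, and an unweighted sum. From Table 2: maximum 14. Two readings are mine: an item counts as discussed if it is rated at least 1, and there is one sum per relative.

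**Step 1: the plan's own figure.** Maximum = items × top category.
- Scale of section 2.4.3: 14 × 3 = 42. This does not reproduce the 14 in Table 2.
- Items scored 0/1: 14 × 1 = 14. This does reproduce it, but it is not the scale that section 2.4.3 describes.

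**Step 2: what a sum can reveal on the 0 to 3 scale.**
- All items addressed: from 14 × 1 = 14 to 14 × 3 = 42.
- At least one item omitted: from 0 to 13 × 3 = 39.
- Overlap: 14 to 39, which is 39 − 14 + 1 = 26 possible values. Each fits both full coverage and an omission.
- Only 40 to 42 guarantees that nothing was omitted. Only 13 or less guarantees that something was.

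**Step 3: comparison of courses.** With k items omitted and the rest full, the sum is 3 × (14 − k).

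| Course | Sum | Share of 42 |
|---|---|---|
| 1 item omitted, rest full | 39 | 92.9% |
| 2 items omitted, rest full | 36 | 85.7% |
| 3 items omitted, rest full | 33 | 78.6% |
| 4 items omitted (such as all worksheets), rest full | 30 | 71.4% |
| 5 items omitted, rest full | 27 | 64.3% |
| All 14 items at level 2 | 28 | 66.7% |

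A course that omits up to four items can therefore outscore one that addresses everything at level 2. At the extreme, all items at level 1 gives 14, while nine items omitted and five full gives 15.

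**Step 4: a count instead of a sum.** If each item is counted as addressed (rated at least 1) or not, full coverage gives 14 and k omissions give 14 − k. A course with an omission then always scores lower. The maximum of this count is 14, the figure in Table 2.

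**Step 5: a stricter meaning of discussed.** If discussed required a rating of 3, full coverage would mean exactly 42 and no course with an omission could reach it. Below 42 the sum would still mix omission with partial delivery. For example, 39 arises from one item omitted (13 × 3) and from three items at level 2 with the rest full (11 × 3 + 3 × 2 = 33 + 6).

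**The case against.** The strongest reply is that the plan already asks the question item by item. The 14 separate ratings show directly which items were rated 0, the sum is only meant to express overall adherence, and nothing says that the item ratings will be withheld. On this view only a reporting detail is left, which an article may leave to a fuller document. Part of this stands: the data are captured and every omission can be recovered, so a reader who infers that omissions will be hidden or lost goes beyond the text. The rest does not stand, because the article is not silent. It names the derived value, and that value does not match the stated question.

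Four further limits are fair.
- A reader might infer that the reversal holds whatever maximum is meant. It does not. If the maximum of 14 in Table 2 means one point per item addressed, two omissions score 12, full coverage scores 14, and the order is right.
- The reversal depends on counting levels 1 and 2 as discussed. Section 2.4.3 labels only 0 and 3. That 0 means not addressed supports this reading but does not settle it.
- A reader might take the Discussion, which expects feedback on topics to add or remove, as relying on the adherence score. That sentence concerns fit and subjective benefit, which Table 2 assesses by interview.
- The courses compared above are constructed to show what the score allows. The documents give no data on how often such patterns occur, and the 26 overlapping values are possible sums, not likely ones.

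**Conclusion.** The point holds for the 0 to 3 scale described in section 2.4.3, with a rating of at least 1 counted as discussed. On those terms the only derived value cannot answer the stated question for any sum from 14 to 39, and it can rank a course without any worksheet (30) above one that addresses all 14 items at level 2 (28).

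Separately, section 2.4.3 (maximum 42) and Table 2 (maximum 14) contradict each other on scoring and must be reconciled. Under 0/1 scoring the reversal disappears.

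Severity is modest. This is a pilot, no threshold or progression rule uses the sum, and the item ratings are retained. The fault lies in the chosen summary, not in the data collection.

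**What to change.** In section 2.4.3 and the Adherence row of Table 2:
1. For each of the 14 items, report the number of relatives rated 0 and the number rated 3.
2. For each relative, report the number of items addressed (rated at least 1, maximum 14) and whether all 14 were addressed. Give the proportion of relatives with all 14.
3. Keep the 0 to 42 sum as a secondary summary and correct its stated maximum, so that 14 refers only to the count of items addressed.
4. State that a rating of at least 1 counts as discussed.

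The cost is some rewording and one small table. The ratings are already collected, so no further data, staff or participants are needed. The only downside is that reported adherence may look less favourable than the sum alone.

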#### 2.4.4. Feasibility of the Study Design

To examine the feasibility of the study, the test battery will also be critically examined regarding length and expected benefit. The feasibility of the study design will be discussed in an expert panel, considering the results of the interviews and the completed questionnaires. In addition, a dropout analysis will be conducted to evaluate the reasons for participants dropping out of the study.

An overview of the feasibility analysis is summarized in Table 2.

## 3. Discussion

Currently, there is limited evidence on the feasibility and effects of interventions for family members of people with Parkinsonism. The existing offers for relatives mostly have a psychoeducational orientation and refer to relatives of patients in a more advanced phase [18,26,27]. There are also approaches offering CBT treatments [28], but these can be quite time-consuming and do not have a preventive focus. Digital support programs based on telemedicine are currently still very rare, but they exist, for example, as a model of a telephone self-help group [30]. However, there are no outreach or preventive programs that specifically address relatives of patients in the early phase of the disease. The aim of the present study is, therefore, to develop a PPSI for relatives of people with Parkinsonism and to determine whether the target group accepts it, and the feasibility regarding its preventive approach and digital implementation is of particular interest. Furthermore, the fit of PPSI and the relatives’ needs, as well as their subjective benefit from the intervention in the current state, should give valuable feedback on which topics to add or remove in a future modified version of the preventive support offer.

Due to the multidimensional character of the burden that relatives of people with Parkinsonism are confronted with, and the rather high sense of stress at the time of diagnosis, implementing a PPSI with similar objectives appears to be an important approach.

Notwithstanding more methodological concerns about the feasibility of such an intervention, there are also technical questions risen by the study presented. It is essential to consider that not all people have access to the technical prerequisites or have the ability or the will to use them. Although technical devices increasingly bridge the existing spatial distance [61], in some areas, access to in-person healthcare services and digital resources are more limited than in others. It remains to be elucidated if the expansion of digital resources, e.g., in rural areas, may counteract these limitations and if our intervention, while disease stages are within a mild to moderate range, can somehow contribute to supporting relatives. Despite the lack of closeness due to familiarity and informal communication within our study, we aim at providing a short and digital intervention that will be easily implemented into the daily life of the relatives [62]. Especially during the COVID-19 pandemic, the easy access from home is a great advantage of the PPSI. In addition, digital communication enables people from rural areas to be reached more easily.

As this pilot study is to be understood as a starting point for further preventative approaches, there are several limitations. Due to the small number of participants (*n* = 20), it is not possible to make reliable statements about the impact of the intervention. Predicting whether a preventive approach can sustainably support relatives to avoid stress and burdens in the long term and in advance would only be possible with a larger study population and a longitudinal design covering several years. Another limitation is that the study period of the intervention is probably too short to capture the effects on the daily life of the family members in the further course of the disease. Therefore, the study will serve as preparation for a large-scale, prospective, randomized, longitudinal controlled clinical trial.

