Family members may experience this role change within disease progression from spouse/relative to caregiver to mere spectator due to changes in their social position, which often encompasses conflicts between patient and relatives [13]. Due to the multidimensional character of the burden, stressful situations of relatives are often not recognized in time, and relatives are therefore also considered as “invisible patients” [14]. The burden of relatives often leads to serious effects on emotional, social, physical, and financial aspects of life as well as the ever-increasing scarcity of time [14,15]. It should also be noted that the burden might not only begin with the diagnosis but with the first, initially unspecific symptoms—even for the relatives. In addition, fear of Parkinsonism/PD progression leads to a further experience of stress [16], so that overall, a significantly increased risk of a reduced quality of life and the development of depression may be the consequences [14,17,18]. However, the sample of our study does not consist exclusively of PD patients but also includes patients with Parkinsonism and their relatives to design a comprehensive support program for relatives with similar experiences.

It is already known that caregivers of patients with Parkinsonism often suffer from severe psychological stress in the late phase of the disease. The burden on caregivers increases with disability and symptoms of Parkinsonism. This is especially relevant for mental health problems such as depression, hallucinations or confusion, and falls [19]. The duration and severity of the disease correlates with the burden on the relatives [20]. They have an increased risk of psychiatric morbidity and persistent distress [21]. However, little is known about the mental attitudes and burdens of family members in the early phase of the disease [14,18]. 

The main study population does not yet correspond to the conventional definition of family caregivers, because they are not yet giving informal care. Therefore, the term “non-caregiving relatives” will be used. The sample thus includes partners of patients with Parkinsonism in the early phase of the disease (Hoehn and Yahr I–II) who live together in one household and who are not yet involved in caregiving.

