## 2. Methods and Study Design

### 2.1. Methods

This study will be conducted at two different locations in Germany, the Department of Neurology of the University Hospital in Marburg (study number: 175/20) and the Department of Medical Psychology/Neuropsychology and Gender Studies of the Faculty of Medicine and the University Hospital Cologne of the University of Cologne (study number: 21-1061). Ten patients and ten relatives will be included as dyads per site so that a total of 20 relatives and 20 patients with Parkinsonism will be included. Recruitment will take place separately at both sites. At the Marburg site, patients and their relatives will be recruited via an internal recruitment system of the Department of Neurology at the University Hospital that lists patients with Parkinsonism who are generally interested in participating in studies. In Cologne, recruitment will be ensured via lists of study participants from previous studies. Further, e-mail distribution lists of self-help groups will be used to increase the recruitment numbers.

Inclusion criteria for patients are: (1)Patients with a clinical diagnosis of Parkinsonism according to the Movement Disorder Society (MDS) criteria [2];(2)Patients aged ≥ 18 years;(3)Hoehn and Yahr stages I–II (OFF-state).

The exclusion criteria for the patients are:(1)Hoehn and Yahr stage ≥ III (OFF-state);(2)No care requirements and/or outpatient or inpatient care;(3)Suspected dementia according to physicians’ reports and (third-party) anamnesis.

Inclusion criteria for non-caregiving relatives are:(1)Partners of people diagnosed with Parkinsonism, living together in the same household;(2)Age ≥ 18 years;(3)Not involved in informal caregiving of the subject with Parkinsonism;(4)Willingness to use telemedicine, availability of a PC or tablet with stable internet connection;(5)No cognitive impairment (operationalized by the Montreal Cognitive Assessment [MoCA] [38], Blind Version ≥ 19; the MoCA Blind, which is suitable for online administration and therefore used here, is reduced to 22 items and converted back to 30 points maximum. A total of 19 points in the MoCA Blind version correspond to 26 points in the original MoCA “Full”);

Exclusion criteria for the relatives are: (1)Own caregiving requirement;(2)Severe depression (operationalized by the Beck’s Depression Inventory-II [BDI-II] ≥ 29 points) [39].

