### 2.3. Intervention Protocol

The PPSI includes three sessions of maximum 50 min at intervals of max. 2 weeks and is to be conducted in an online meeting with the relative and a trained and supervised advisor (at least B.Sc. in Psychology or related discipline). A licensed therapist [name] trains new advisors on how to use the manual and supervises the PPSI on a weekly basis. The Red Medical platform (https://www.redmedical.de/ accessed on 3 March 2022) ensures the General Data Protection Regulation (GDPR)-compliant implementation of video consultations with overall end-to-end encryption so that conversations remain strictly confidential and cannot be accessed by third parties. The cognitive–behavioral therapy-based intervention consists of three sessions, which include the following elements: standardized elements with knowledge transfer, personalized elements addressing the individual’s perspective, and exercises to apply the knowledge on an individual basis. As support, working sheets will be used, which also serve for future implementation of the intervention elements in the study participants’ everyday life.

At a content level, the mental health of the relatives is the focus of the intervention. Each session deals with a psychological focus area. The areas are based on protective factors in prevention of mental disorders, e.g., ability to manage stress, empowerment, and social participation [40]. The most relevant areas were selected via expert panels ([name]) with regard to the most relevant issues in giving care to patients with Parkinsonism. The overarching goal is to provide self-management strategies for relatives of PD patients in the sense of “empowerment”, which can be applied at a later stage of the disease.

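### Acceptance of the digital offer is observed only among relatives already willing and equipped to use it, but the conclusion is worded for the whole target group

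*Protocol article*

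**What the plan says.** The Discussion sets the aim of finding out whether the target group accepts the programme and adds that "the feasibility regarding its preventive approach and digital implementation is of particular interest". The Conclusions repeat, without qualification, that acceptance by the target group will become apparent.

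The Introduction describes the population by relationship, disease stage, shared household and absence of caregiving: "The sample thus includes partners of patients with Parkinsonism in the early phase of the disease (Hoehn and Yahr I–II". It sets no digital condition. Section 2.1 adds one as inclusion criterion (4) for relatives: "Willingness to use telemedicine, availability of a PC or tablet with stable internet connection".

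Section 2.3 says the intervention "is to be conducted in an online meeting with the relative and a trained and supervised advisor". In Table 2 the acceptance outcome has three items, among them the target group's willingness to take part and "Evaluation of the digital intervention". The only instrument listed for acceptance is the interview. Under Section 2.4.2 the interviews are "conducted at two time points via an online consultation with relatives immediately after the intervention (t1) and 6 weeks post-intervention (t2".

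Two other sources bear on the digital format. In Section 2.4.3 relatives rate content and delivery after each session in the workbook. In Section 2.4.4 a dropout analysis looks at reasons for leaving. The Discussion also grants that "not all people have access to the technical prerequisites or have the ability or the will to use them".

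**The concern.** Part of what is to be found out is required at entry. A relative who does not want telemedicine, or has no device or stable connection, has in effect not accepted the digital offer, but is removed before acceptance is assessed. The Discussion recognises that such people exist. It does not say that criterion (4) takes them out of the acceptance result, and this selection is not among the limitations it lists, which are the small sample and the short study period.

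A weaker selection follows at data collection. The instrument for judging the digital format uses the same kind of channel as the format itself. A relative who gives up on video is less likely to be interviewed by video.

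The Conclusions say the findings will be used to modify the intervention and the design, and that a multicentre randomised trial will be based on this. A favourable acceptance result with no account of who was screened out could make recruitment to that trial look easier, and the reach of the offer wider, than the pilot can show.

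**Working it through.** **Plan's own figure.** Section 2.1 gives ten relatives at each of two sites: 2 × 10 = 20. This reproduces the stated total. No proportion, threshold or precision is planned for acceptance, so there is no further figure to reproduce.

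**Who can be seen, and where.** The Discussion names three reasons why digital delivery may not reach people: access, ability and will.

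| Reason | Screened by criterion (4)? | Visible among the 20? |
|---|---|---|
| No will at entry | Yes | No |
| No device or stable connection at entry | Yes | No |
| Lacking ability | No | Yes, in part |
| Connection or willingness fails after entry | No | Yes, in part |

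For the last two rows there are three routes into the results:

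- Workbook ratings. These are given after a session, so a session that never took place goes unrated.
- Dropout analysis. Table 2 places it under feasibility of the study design, not under acceptance.
- The interview, held online.

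**Size of the first gap.** The documents give no rate, so let q be the share of otherwise eligible relatives who fail only criterion (4), assumed to lie between 10% and 40%. The number of otherwise eligible relatives needed to enrol 20 is 20/(1 − q), rounded up. The chance that 20 relatives taken without the criterion would include at least one such person is 1 − (1 − q)^20. With the criterion it is 0.

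| q | Needed to enrol 20 | Turned away | Chance of at least one in 20 without (4) |
|---|---|---|---|
| 10% | 23 | 3 | 0.88 |
| 20% | 25 | 5 | 0.99 |
| 30% | 29 | 9 | 0.999 |
| 40% | 34 | 14 | 1.00 |

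**Failure after entry.** Let f be the rate of digital failure among enrolled relatives, again assumed. The chance of at least one case among 20 is 1 − (1 − f)^20:

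- f = 5%: 0.64
- f = 10%: 0.88
- f = 15%: 0.96
- f = 20%: 0.99

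Such cases are likely to occur in the study. Whether they reach the acceptance result depends on the three routes above.

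**The case against.** The strongest reply has four parts.

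1. *Requiring a device and a connection is ordinary in a telemedicine pilot, since nobody can receive the sessions otherwise.* This stands. The criterion is not at fault, only the unrestricted conclusion.

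2. *The Introduction defines feasibility of the intervention as acceptability, fit and subjective benefit, which are recipients' experiences, so population reach was never an outcome.* This stands in part. But Table 2 lists the target group's willingness to take part as an acceptance item, and the Abstract makes demand for a low-threshold offer the main objective. Both go beyond the experience of those who passed the filter.

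3. *The access problem is acknowledged in the Discussion.* It is, in general terms, but it is not connected to criterion (4) or to the acceptance result.

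4. *A screening log and a fallback interview mode may be in the full protocol, which is not shown.* That is possible, and their absence from the article is not held against it. The point rests on what the article states: the criterion, the online interview and the wording of the conclusion.

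A reader might go further and infer that failure of digital delivery can hardly appear in the results at all. The documents do not support that. Ability is not screened, delivery is rated after each session, reasons for dropout are evaluated, and neither the workbook nor the dropout analysis is described as depending on the online interview.

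A reader might also put a confidence interval on a perfect result among the 20 and compare it with a lower value in the whole target group. That does not fit either: Section 2.4.2 plans a qualitative content analysis of the interviews, and no such proportion is to be reported.

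**Conclusion.** The point holds in a limited form and is minor. Non-acceptance for lack of will or access at entry cannot be seen among the 20 relatives, and this follows from criterion (4) alone, with no assumption about rates. Failure after entry is observable in part. The online interview tends to lose the relatives best placed to describe it; this is a judgement about likely behaviour, not something the documents quantify. Both effects favour a finding that the format is accepted.

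The number of relatives left out of view is unknown. The 3 to 14 turned away for 20 enrolled rest wholly on the assumed range of 10% to 40% and only show that the count would be worth having.

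**What to change.** Keep criterion (4) and make three changes.

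1. At screening, count relatives who meet every other criterion but fail (4), by reason (no device, no stable connection, unwilling). Report this count next to the acceptance result. If the full protocol already provides a screening log, only the reporting needs to be added.
2. In Section 2.4.2, allow the t1 and t2 interviews by telephone for relatives whose connection fails or who give up video, including those who drop out.
3. In the Discussion and Conclusions, limit the statement on acceptance to relatives willing to use and equipped for telemedicine, and name criterion (4) among the limitations.

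The cost is a short tally at each site, one sentence on interview mode and one on scope. The drawbacks are a few interviews held in a different mode, to be marked as such in the analysis, and a less favourable headline.
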